### Strategies to improve adherence to interventions {11c}

Adjusting IP administration to patient’s swallowing capability and GI function: During the study, we expect following patients may be enrolled. Those conscious and able to swallow will be given study medication in black mug to swallow. Patients unable to swallow with a nasogastric tube in place will be given the IP via the NG tube reconstituted in sterile water and flushed as per local NG medication guideline. Administration of the IP is temporarily omitted in patients who are unable to swallow but without NG access or do not tolerate any enteral intake (such as patients in profound shock). As soon as the condition preventing IP administration is eliminated, resumption of study medication follows the guidance for day 1.

The role of a dedicated unblinded study pharmacist in each centre is not only to prepare and mask the study drub, but also to ensure its timely administration. If, for any reason, the dose of study drug is omitted, the reason will be documented and appropriate reloading procedure applied for the next dose.

### Relevant concomitant care permitted or prohibited during the trial {11d}

There is no study-specific restriction apart from open-label use of hydroxychloroquine and macrolide antibiotics. All drugs known to prolong QTc must be used with caution. The standard of care also may change in time during the course of the study, for example, if new evidence emerges and changes the state-of-the art treatment recommendations. Any such event will trigger emergency steering committee meeting, and decision will be taken about further action. Research Ethics Board (REB) and regulatory authorities will be notified immediately about the decision taken (see below).

### Provisions for post-trial care {30}

During and after 5 days of study drug administration as well as during the rest of 90 days of follow up, trial participants in all treatment arms will be receiving standard of care, delivered by teams not directly involved in the study and not influenced by their participation in the trial.

### Outcomes {12}

#### Primary outcome

Composite percentage of patients alive and not on end-of-life pathway who are free of mechanical ventilation at day 14 (see detailed explanation below)

#### Secondary outcomes

Composite percentage of patients alive and not on end-of-life pathway who are free of mechanical ventilation at day 14 in the subgroup of patients without the need of mechanical ventilation at baselineLength of stay in intensive care unitMortality at day 28 and 90

#### Tertiary (exploratory) outcomes

Viral load at day 8 (no. of viral RNA copies/millilitre of blood)Proportion of patients alive and with negative rtPCR nasal swab at D14Difference of fraction of inspired oxygen (FiO_2_) between days 0 and 7.Difference of respiratory system compliance between days 0 and 7.Pharmacokinetic profiles of investigational drugs after oral versus nasogastric administration

Comment to primary outcome: Because the biological plausibility of this trial is in the possibility that hydroxychloroquine inhibits virus replication and azithromycin potentially enhances this, the primary outcome was chosen to prove or disprove that decrease virus replication reduces the damage to the lungs and hence less patients die or progress into frank acquired respiratory distress syndrome (ARDS) with the need of protracted mechanical ventilation and often resulting in delayed death or failed functional outcomes [10].

Mechanical ventilation is defined as the need at any time during the last 24 h of positive pressure ventilation, shall it be ventilation via endotracheal tube, tracheostomy or non-invasive ventilation delivered by a tightly fitting mask. On the contrary, high-flow nasal oxygen support, positive airway pressure via a helmet or uninterrupted spontaneous ventilation via tracheostomy (including with the use of Ayre T-piece with or without positive end-expiratory pressure ventil) is not considered mechanical ventilation. End-of-life care is defined as compassionate care in patients nearing end-of life. Isolated do-not-resuscitate or do-not-reintubate decisions or other ceilings of treatments are not considered end-of-life care, provided that decision is made to continue current level of treatment and actively support patient’s improvements.

### Participant timeline {13}

The patient will have study visits daily as long as he/she stays on ICU or until day 14, whichever occurs earlier. Primary outcome will be recorded at day 14 after enrolment, in hospitalised patients during study visit, in discharged patients over the phone. At discharge from ICU (which may occur before or after day 14) as summary complications and concomitant treatments will be recorded in eCRF. Study subjects will be followed up at days 28 and 90. Details of study procedures are summarised in Fig. 1.

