### Plans to promote participant retention and complete follow-up {18b}

Day 28 and 90 follow-ups will be performed as physical visit in hospitalised patients or a telephone interview. Vital status, mechanical ventilation status and whether the patient is still in ICU and in hospital are all very robust data that can be obtained with minimum equipoise even over the phone. In addition, the protocol recommends that patient’s self-reported data are checked against hospital notes and/or clinical information system.

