### Interim analyses {21b}

We plan to perform an interim analysis after the primary outcome is known for the 120th subject. As mentioned above, primary and secondary outcomes will only be calculated in patients with confirmed COVID-19 infection who received at least one dose of IP. Adverse events will be calculated in all randomised patients (intention-to-treat analysis).

All suspected unexpected serious adverse events (SUSARs) will be reported to both REB and to the steering committee, who may decide to stop the trial for safety concerns. Apart from safety, other reasons for stopping the trial are as follows:
Emergence of new data (e.g., publication of the results of a big RCT) that may lead the continuation of the trial unethical. This may be due to safety concerns of the placebo group (in case a strong clinical benefit is proven by other trials) or any of the interventional groups (e.g., if harm is reported by other trials). This rule also applies for emergence of a new treatment.After interim analysis: The steering committee will review primary outcomes and the summary of adverse events in all 3 groups (labelled as A, B, and C) whilst still blinded to treatment allocation. The treatment can be stopped if the following criteria are fulfilled:There is a significant difference in the primary outcome at *p* < 0.017 in between the groups.Futility: The futility criterion is not binding for the steering committee. Based on available data, the study statistician calculates the probability of being able to prove the null hypothesis with achieving the target number of subjects and the probability of type II error made by stopping the trial prematurely.Safety: In case the number of adverse events in one or more treatment groups is found uneven or unacceptably high.Details of pharmacovigilance are described in a dedicated section below.

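### Scheduled observation for harms follows ICU stay, even during the 5-day drug course, while the interim safety criterion compares raw adverse-event counts with no common window or exposure time

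*Protocol article*

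**What the plan says.** **Visits.** Protocol article, Participant timeline {13}: "The patient will have study visits daily as long as he/she stays on ICU or until day 14, whichever occurs earlier". The same section adds: "At discharge from ICU (which may occur before or after day 14) as summary complications and concomitant treatments will be recorded in eCRF".

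**Later contacts.** Also in {13}: "Primary outcome will be recorded at day 14 after enrolment, in hospitalised patients during study visit, in discharged patients over the phone", and "Study subjects will be followed up at days 28 and 90". Section {18b} describes the day 28 and 90 data: "Vital status, mechanical ventilation status and whether the patient is still in ICU and in hospital are all very robust data". Adverse events are not among the items it names. It also recommends checking self-reported data against hospital records.

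**Dosing.** Intervention description {11a} sets out dosing for day 1 and days 2 to 5. Provisions for post-trial care {30} refers to care "During and after 5 days of study drug administration". Neither section ties the course to ICU stay.

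**Use of the data.** Interim analyses {21b} counts adverse events in all randomised patients and lists safety among the reasons for stopping: "In case the number of adverse events in one or more treatment groups is found uneven or unacceptably high". It gives no observation window, rate or threshold.

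**ICU stay as an outcome.** Outcomes {12} lists length of ICU stay as a secondary outcome.

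**The concern.** Two things that the protocol does state do not fit together. Routine contact, and the one scheduled record of complications, last as long as the ICU stay (daily visits up to day 14). The safety comparison uses numbers of events as if every patient had been watched for the same time.

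ICU stay occurs after randomisation, and the trial's hypothesis is that treatment changes the respiratory course. An arm with shorter stays, or with earlier deaths, would tend to show fewer events at the same underlying rate; an arm with longer stays would look more toxic. Section {22} adds to this for deaths: a death attributed to the underlying disease is not counted as a serious adverse event, so earlier deaths can remove both observation time and events.

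There is also a gap during treatment. The comments to the eligibility criteria allow ICU to include high-dependency and level 2 units, and patients need not be ventilated, so some may leave before their course ends. No daily study visit then covers the remaining dosing days. The Discussion names QT prolongation and arrhythmia as possible harms.

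At stake is the reliability of one of the interim stopping criteria, which could miss a real imbalance or show a spurious one.

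**Working it through.** The plan gives no figure on this point, so there is none to reproduce. The check sets the sections side by side and then illustrates the mechanism.

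**1. The sections together**

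| Item | What is fixed | Section |
|---|---|---|
| Daily visits | End at ICU discharge or day 14, whichever is earlier | {13} |
| Complications summary | At ICU discharge, before or after day 14 | {13} |
| Drug course | 5 days, not tied to ICU stay | {11a}, {30} |
| Day 14 contact | For the primary outcome; by phone after discharge | {13} |
| Days 28 and 90 | Vital, ventilation, ICU and hospital status named | {18b} |
| Safety criterion | Number of adverse events per group | {21b} |
| End of adverse-event collection | Not stated in the text; schedule figure not shown | – |

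For a patient discharged on day 3, the schedule has no daily visit on days 4 and 5, although doses are due. For a patient staying 20 days, daily visits stop at day 14 but the complications summary is made at day 20. Because the summary can fall after day 14, it widens the inequality between short and long stays.

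**2. Simple illustration (rate and days assumed, not in the documents)**

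Expected events per arm = patients × rate per day × mean observed days. The interim comes when the primary outcome is known for the 120th subject; at 1:1:1 that is 120 / 3 = 40 per arm. Assume the same true rate, 0.05 per day, in both arms.

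- 10 versus 7 days: 40 × 0.05 × 10 = 20, against 40 × 0.05 × 7 = 14. Ratio 0.70.
- 9 versus 8 days: 40 × 0.05 × 9 = 18, against 40 × 0.05 × 8 = 16. Ratio 0.89.

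Neither gap is statistically notable (exact two-sided p = 0.39 and 0.86), but the criterion asks whether numbers are uneven and sets no test or threshold.

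**3. Illustration using the plan's own outcome rates**

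Sample size {14} assumes the primary outcome in 25% of control patients and 50% under treatment. Assume events are captured only up to ICU discharge, with mean observed days g in patients who reach the outcome and b in the others.

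- Control: 0.25g + 0.75b. Active: 0.50g + 0.50b.
- b = 14, g = 4: 11.5 versus 9.0 days, ratio 0.78.
- b = 14, g = 10: 13.0 versus 12.0 days, ratio 0.92.
- b = 28, g = 4 (summary made after day 14): 22.0 versus 16.0 days, ratio 0.73.

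Over g = 4 to 10 and b = 14 to 28, active-arm counts are 8% to 27% lower with no true difference in rate. With observation capped at 14 days (b = 14) the range is 8% to 22%.

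**4. Direction is not fixed**

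The ratio is 1 when g = b and exceeds 1 when b is below g. Section {14} also cites 67% mortality within 2 weeks, so b could be short. With g = 10 and b = 7: control 2.5 + 5.25 = 7.75 days, active 5.0 + 3.5 = 8.5 days, ratio 1.10. The count can therefore mislead either way. If all events were captured over one fixed window with no loss of time to death, the ratio would be 1.

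**The case against.** A reader might infer that adverse-event collection stops at ICU discharge. The documents do not say that. Section {13} schedules visits and a complications summary; it does not define the adverse-event window. The schedule figure is not shown, and the start and end of collection are details that an article may leave to the full protocol. Prompt SUSAR reporting in {22} has no ICU limit, and {11b} continues adverse-event collection even after withdrawal for a negative test. Contact continues on days 14, 28 and 90, by visit for inpatients, with a recommended check against hospital notes. Under {11c}, the study pharmacist must ensure timely dosing, and reasons for omitted doses are documented. This part of the objection stands.

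A reader might also infer that an uneven count stops the trial. It does not: {21b} says that treatment can be stopped, and under {5d} the steering committee decides by majority vote. Nothing prevents it from considering exposure. This also stands.

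The broad ICU definition cuts both ways. It admits milder patients, but step-down to a level 2 unit need not count as leaving ICU. How often patients would leave with doses still due is unknown. The constant daily rate in the illustrations is also a simplification, since dosing lasts 5 days and a gap between 7 and 10 days falls after it.

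The objection does not remove the mismatch. The later contacts are described for the primary outcome and for status, not for adverse events. SUSAR reporting covers unexpected reactions, so it is a weak route for harms the protocol already names. The committee cannot easily correct for exposure if counts reach it without exposure time.

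**Conclusion.** The point holds as a cheap improvement. As written, scheduled ascertainment of harms follows ICU stay with no exception for dosing days, and the interim safety criterion compares numbers of events with no common window or exposure time. ICU stay is itself an outcome, so equal rates can produce unequal counts.

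The size is illustrative only: 20 versus 14 events at about 40 per arm for 10 versus 7 observed days, and 18 versus 16 for 9 versus 8. Scaling the first case to 80 per arm (40 versus 28) would overstate what the committee sees at the interim. These figures assume a constant rate of 0.05 per day and that events outside the observed period are missed. With the plan's 25% and 50% outcome rates and assumed stays, the spurious reduction is 8% to 27%; with short stays ended by death, the direction can reverse.

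The documents do not support saying that adverse-event collection ends at ICU discharge, or that the count alone stops the trial. It is one of several criteria that the committee weighs. If the full protocol or the schedule figure states a fixed window, that window should be reconciled with {13} and carried into {21b}.

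**What to change.** Reconcile {11a}, {13}, {30} and {21b} as follows.

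- **{13}:** state one adverse-event collection window, starting at randomisation, for all randomised patients wherever they are. Day 14 is a natural end, because a contact already exists there and {18b} already recommends checking hospital notes. State that every dosing day is covered by a study visit or note review, including after ICU discharge.
- **{21b}:** for each group, present the number of patients with at least one event in that window and the number of events per patient-day at risk, with the patient-days shown. Both are needed: the first is easy to read but does not account for truncation by death; the second does, but assumes a roughly steady rate.

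The cost is amendment wording and a small amount of extra note review by the existing research nurses for patients who leave ICU early. Treatment, sample size and the committee's discretion are unchanged.

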**Fig. 1 Fig1:**
[figure not shown]
Overview of study procedures. Follow-up can be performed over the phone in outpatients. Note: D/C, discharge from ICU; F-up, follow up; LFT, liver function tests; MV, mechanical ventilation; SOFA, Sequential Organ Failure Assessment. *Primary outcome = being alive and off MV at D14. **This includes pregnancy test if applicable

### Sample size {14}

Based on data from Wuhan [6] and Washington [7], where 67% of patients had died within 2 weeks and half of the survivors needed protracted mechanical ventilation, we assume the incidence of the primary outcome in the control group (i.e., being alive and off the ventilator in 2 weeks) to be 25%. The study gives us 80% chance to detect the increase of the primary outcome to 50% in one or both interventional groups at *p* < 0.017 with 74 patients in each arm. In order to compensate for drop-out and loss of follow up, we plan to enrol 240 subjects into the study. No replacement of subjects who dropped out from the study is planned.

### Recruitment {15}

In each study site, a dedicated investigator with the help of the centre coordinator will identify eligible patients every day during morning rounds with the aim to enrol all eligible patients. The central study coordinator will ensure resources are available in all centres at all times including surges of patients during local infection outbreaks.

## Assignment of interventions: allocation

### Sequence generation {16a}

Randomisation procedure will be performed in blocks of 6 and stratified for study centre and age (> 70 or ≤ 70 years). Electronic Case Record Form (eCRF) will perform randomisation using random sequence script in software R and generate medication code. Rationale: Patient’s age is the single most powerful predictor of outcome and stratifying randomisation and stratification decreases the probability of treatment groups being of different age at baseline by chance. In analogy, study centres may vary in the use of non-protocolised treatments, which could bias the results. Randomisation blocking and stratification are described in the protocol and hence will not be concealed for study site investigators, but the computer-generated randomisation sequence will be concealed for all study personnel but the statistician (PW). This prevents any predictability of treatment allocation for subjects before randomisation.

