## Trial design {8}

Prospective, randomised (1:1:1), placebo and active-comparator controlled, parallel group, double-blind exploratory trial.

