## Methods: participants, interventions and outcomes

### Study setting {9}

This is a multi-centre trial conducted in intensive care units of 8 hospitals (6 university hospitals and 2 district general hospitals) in the Czech Republic. The updated list of centres including contact details of site investigators can be found in the Appendix.

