### Concealment mechanism {16b}

Only the unblinded member of the research staff will perform the randomisation procedure. The interface of eCRF will conceal subject treatment allocation to all other personnel involved in the study. Subject allocation report will be placed in an opaque sealed envelope into patients’ medical notes in care emergency unblinding is needed.

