### Implementation {16c}

All newly admitted patients in each participating ICU will be screened daily for eligibility and recorded in a screening log in eCRF. All potentially eligible patients or their representatives will be approached by the site investigator and offered participation in the trial. Those consenting will be reported back to the unblinded member of research staff who will perform randomisation procedure and record baseline data in eCRF. All data will be recorded by site investigators into patients’ medical chart and by research nurses into a custom-built eCRF. Follow-up visits or phone calls will be performed by research nurses.

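### Allocation is not unpredictable for the unblinded person who randomises: with fixed, disclosed blocks of 6, about 16 to 20% of allocations are certain to that person in advance

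*Protocol article*

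**What the plan says.** All references are to the Protocol article.

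- Sequence generation {16a}: "Randomisation procedure will be performed in blocks of 6 and stratified for study centre and age". Only one block size is given. The section says that site investigators know the blocking and stratification, and that only the statistician knows the generated sequence. It concludes: "This prevents any predictability of treatment allocation for subjects before randomisation".
- Trial design {8}: the ratio is 1:1:1, so each block of 6 holds two allocations per arm.
- Concealment mechanism {16b}: "Only the unblinded member of the research staff will perform the randomisation procedure". The eCRF hides the allocation from everyone else.
- Implementation {16c}: site investigators approach patients and offer participation. "Those consenting will be reported back to the unblinded member of research staff", who then randomises and records baseline data.
- Who will be blinded {17a}: an unblinded member of research staff in each centre also prepares the study drug. Site investigators, research nurses and coordinators are blinded. Strategies to improve adherence {11c} likewise puts an unblinded pharmacist in each centre.

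**The concern.** Concealing the list protects future allocations only from people who cannot reconstruct them. Someone who knows the block size and has seen the earlier allocations in a block can subtract them from two per arm and read off what is left. The plan creates such a person: the one who randomises is the one to whom the eCRF shows the result.

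That person stands between consent and allocation. With the next arm known or partly known, they could delay or withhold the randomisation of a consented patient, or tell a recruiter what comes next. Either would make the arms differ at baseline in ways that adjustment for measured covariates may not repair. The stated safeguard therefore fails at the one point in the process where allocations are visible.

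**Working it through.** The plan gives no figure for predictability, so there is none to reproduce. The check counts what an informed person can deduce.

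**Inputs**

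- Block of 6, ratio 2:2:2 (Sequence generation {16a}; Trial design {8}).
- 8 centres (Study setting {9}) × 2 age groups = 16 strata.
- 240 planned patients (Sample size {14}); 240 / 16 = 15 per stratum on average.
- Assumption: the person knows the block size and every earlier allocation in the current block of that stratum.

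**Step 1: complete blocks.** A 2:2:2 block has 6!/(2!·2!·2!) = 90 equally likely orderings. Enumerating them gives, by position:

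| Position | Allocation certain | At least one arm ruled out | Best guess right |
|---|---|---|---|
| 1 | 0 | 0 | 33.3% |
| 2 | 0 | 0 | 40.0% |
| 3 | 0 | 20% | 50.0% |
| 4 | 0 | 60% | 53.3% |
| 5 | 20% | 100% | 60.0% |
| 6 | 100% | 100% | 100% |
| Mean | 20.0% | 46.7% | 56.1% |

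Two entries can be checked by hand.

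- Position 5 is certain when the last two places hold the same arm. Given the arm in one place, 1 of the other 5 allocations matches it, so the probability is 1/5.
- At position 4, the first three allocations are all different with probability (4/5)(2/4) = 0.4, and the best guess is then 1/3. Otherwise it is 2/3. So 0.4 × 1/3 + 0.6 × 2/3 = 0.533.

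Certain allocations per block: 0.2 + 1 = 1.2 of 6, or 20%.

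**Step 2: the planned stratum size.** Fifteen patients make two full blocks plus three.

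- Certain: 2 × 1.2 + 0 = 2.4 of 15 = 16%. Over 16 strata, 16 × 2.4 = 38.4, about 38 of 240.
- Best guess: the position values sum to 3.367 per full block, so (2 × 3.367 + 0.333 + 0.400 + 0.500) / 15 = 53.1%.

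If every stratum ended on a full block, the certain count would be 0.20 × 240 = 48. That is an upper limit. Unequal strata with unfinished blocks can fall below 38.

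**Step 3: effect of varying the block size.** This was simulated with 20,000 runs of the first 15 patients in a stratum and block sizes drawn with equal probability. The person guesses optimally, knowing the set of sizes but not the current one.

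| Scheme | Allocation certain | Best guess right |
|---|---|---|
| Fixed 6 | 16.0% | 53.1% |
| 6 or 9 | 4.4% | 52.7% |
| 3, 6 or 9 | 2.8% | 54.0% |

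The fixed-6 row agrees with Step 2. Over 240 patients the certain count falls from about 38 to about 11 (0.044 × 240) or 7 (0.028 × 240). The best-guess rate hardly moves.

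**The case against.** The strongest reply is that the people who choose patients cannot predict anything. Blinded investigators identify, approach and consent patients, and Recruitment {15} aims at every eligible patient. The unblinded person receives only those who have already consented. Screened patients are logged in the eCRF, so a consented patient who was never randomised could be traced. Enrolment must fall within 24 h of ICU admission, which limits delay. All of this stands. A reader might infer that recruitment itself is compromised or that selection bias is built in. The documents do not support that: bias needs the unblinded person to act on the knowledge or pass it on.

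The claim can also be read as a statement about site investigators only, since the sentence before it contrasts what they know with what is concealed. On that reading it broadly holds. But the text speaks of all study personnel and excludes any predictability, so the wording does not carry the limit.

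No single sentence says that the randomiser is local and also prepares the drug. Sections {11c} and {17a} point that way, the latter through the word also, but it is an inference. The arithmetic does not need it. It needs only that the person who randomises sees the earlier allocations, and {16b} implies this.

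One might add that emergency unblinding exposes blocks to investigators. It reveals one patient's arm. An investigator blind to the rest of the block cannot deduce the next allocation from that, so it adds little.

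**Conclusion.** The point holds in a limited form. The claim of no predictability is false for the person who performs randomisation. For that person 20% of allocations in complete blocks are certain beforehand, or 16% (about 38 of 240) at 15 patients per stratum, and the best guess is right 53 to 56% of the time against 33%. The figure of 48 of 240 is tempting but requires every block to fill, which an average of 15 per stratum does not suggest.

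These figures assume that one person sees all earlier allocations in a stratum, and the 16% further assumes strata of equal size. They describe that person's knowledge, not the investigators', and are not estimates of bias. The risk to the trial is conditional and moderate. The plan should be changed because the wording is wrong as it stands and most of the certainty can be removed at small cost.

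**What to change.** 1. For blocks not yet opened, draw block sizes at random (for example 6 and 9, or 3, 6 and 9) within the same centre-by-age strata. Only the statistician should know the sizes, and they should not appear in site-facing text.
2. Delete the no-predictability sentence, or restrict it to staff who are blinded to allocation. Say openly that the person who randomises may infer some later allocations.

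The first change removes most certain predictions but not informed guessing, so the second is needed with it. Removing the rest would require that the person who randomises does not see past allocations.

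Cost: an edit to the R randomisation script, slightly looser balance within strata, and a protocol amendment. The trial is recruiting (Trial status), and section {25} requires submission to the central and local REBs and to SUKL before implementation. No extra patients are needed. Blocks already opened keep their present predictability.
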